### Statistical Analysis

#### Clinical Data Analysis

The statistical analysis plan will be determined before the initiation of the study. Demographic characteristics, baseline characteristics, and efficacy indicators will be analyzed using SPSS 25.0 software according to Full Analysis Set (FAS) and Per Protocol Set (PPS). The missing values in the FAS will be treated using the Last Observation Carried Forward method with the data closest to the first observation. The research results will be mainly based on the results of the FAS, and the results of PPS will be used as auxiliary references.

Continuous variables of normal distribution will be represented by 95% confidence interval, mean and standard deviation. Continuous variables of non-normal distribution will be described by median and inter-quartile range. Classification variables will be described in terms of percentage and frequency. The qualitative data will be compared using the chi-square test. If the quantitative data are normally distributed, we will use the analysis of variance to detect the difference between groups; otherwise, the Mann-Whitney test will be used. The data table will be recorded anonymously and statistical analysis will be carried out by independent statisticians who are blinded to the allocation.

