### Sample Size, Randomization and Blinding

#### Calculation of Sample Size

The formula for calculating the sample size in clinical trials is not available in the presented study. In most similar studies devoted to microRNAs and gut microbiota, the sample size is mainly 30 cases to obtain outcomes with statistical significance (24). Considering the need for further miRNA validation in an expanded cohort plus a drop-out rate of 20%, the sample size in this setting is determined to be 80 cases (40 per). Accordingly, the number of healthy volunteers will be 40 cases, with matched demographic characteristics such as age and sex.

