#### Primary Outcome Measurement

The primary outcome will be the proportion of patients with 3 or more mean weekly complete SBMs (CSBMs) over weeks 1–4 and 5–8. The mean weekly CSBMs will be calculated by dividing the sum of the CSBMs during weeks 1–4 or 5–8 by 4. The proportion of patients with mean weekly CSBMs ≥ 3 will be divided by the number of observed participants in this group, and then multiplied by 100% (11). One SBM refers to the bowel movement that occurs in the absence of rescue medicine, or other auxiliary techniques (laxatives, suppositories usage, or manual assistance) within the preceding 24 h; while one CSBM refers to an SBM with the sensation of complete evacuation.

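### The missing-data rule for the primary responder outcome contradicts itself, and its observed-participants denominator does not fit the imputed full analysis set

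*Protocol article*

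**What the plan says.** All references are to the protocol article.

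- **Primary Outcome Measurement** defines the endpoint as follows: "The primary outcome will be the proportion of patients with 3 or more mean weekly complete SBMs (CSBMs) over weeks 1–4 and 5–8". Each weekly mean comes from "dividing the sum of the CSBMs during weeks 1–4 or 5–8 by 4". For the rate, the responders "will be divided by the number of observed participants in this group".
- **Secondary Outcome Measurement, item 1:** the responder outcome based on an increase of at least 1 CSBM per week uses the same construction, over the observed cases in the group.
- **Clinical Data Analysis:** "The research results will be mainly based on the results of the FAS", with the per-protocol set as support. Missing FAS values are handled "using the Last Observation Carried Forward method with the data closest to the first observation". For the binary outcome, "The qualitative data will be compared using the chi-square test".
- **Inclusion Criteria:** two or fewer CSBMs per week during run-in.
- **Trial Design:** four weeks of treatment, then four weeks of follow-up. Weeks 5–8 are therefore off treatment.
- **Calculation of Sample Size:** 40 patients per arm, with a 20% allowance for dropout.

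**The concern.** There are two defects, both in rules the article states.

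First, LOCF by definition carries the latest available value. The value nearest the first observation is the baseline or the earliest post-baseline value. An analyst cannot follow both halves of the sentence, and for this endpoint the choice can decide whether a participant counts as a responder. Even read as ordinary LOCF, the rule fits poorly. It fills weeks 5–8 with on-treatment counts and so assumes the persistence that this window is meant to test.

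Second, once missing values in the FAS are imputed, nobody in that set needs to leave the denominator for being unobserved. A denominator of observed participants reads as an available-case analysis, which is a different analysis from the one named as the main one.

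At stake is the primary result. If the rule is open, it can be settled after the dropout pattern is known.

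**Working it through.** **Inputs from the article.** Baseline b ≤ 2 CSBMs per week; response = four-week mean ≥ 3; 40 per arm; 20% dropout, so 0.20 × 40 = 8 lost and 32 left per arm. The article gives no responder rates and no dropout pattern, so those below are assumptions. It also states no figure for this point that could be reproduced.

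**1. One participant, weeks 5–8 wholly missing.** Assume baseline 1, week 1 = 3, week 2 = 4, then loss to follow-up.

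| Reading | Weeks 1–4 mean | Weeks 5–8 mean |
|---|---|---|
| Last value carried | (3+4+4+4)/4 = 3.75, responder | 4, responder |
| First post-baseline value carried | (3+4+3+3)/4 = 3.25, responder | 3, responder |
| Baseline carried | (3+4+1+1)/4 = 2.25, non-responder | 1, non-responder |
| Complete-window denominator | excluded | excluded |

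For a wholly missing weeks 5–8 window the baseline reading gives a mean of b ≤ 2 < 3, so it is always a non-response. True LOCF gives a response whenever the last recorded week has 3 or more CSBMs.

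**2. Denominator.** Assume 12 responders and 8 dropouts in an arm: 12/32 = 37.5% against 12/40 = 30%. If both arms lose the same number, both rates scale by 40/32 and their ratio is unchanged. In an extreme case each arm has 12 responders in 40, but one loses 12 non-responders and the other 4. The observed rates are then 12/28 = 42.9% and 12/36 = 33.3%, a difference of 9.5 points where the full arms do not differ.

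**3. Effect on the test.** Assume 13/32 against 6/32 responders among completers, 8 dropouts per arm, and an uncorrected chi-square test.

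| Rule | Verum | Sham | Difference | p |
|---|---|---|---|---|
| Observed denominator | 13/32 = 40.6% | 6/32 = 18.8% | 21.9 points | 0.055 |
| All 40, dropouts non-responders | 13/40 = 32.5% | 6/40 = 15.0% | 17.5 points | 0.066 |
| True LOCF, 4/8 and 2/8 dropouts responding at last value | 17/40 = 42.5% | 8/40 = 20.0% | 22.5 points | 0.030 |

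**4. Simulated weeks 5–8 difference, in points.** Assumptions: gamma-Poisson weekly counts, means 2.8 (verum) and 1.9 (sham) in weeks 5–8, 20% dropout per arm.

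| Dropout pattern | True LOCF | First value | Baseline | Missing as zero | Observed |
|---|---|---|---|---|---|
| Unrelated to response | 22.0 | 21.5 | 18.8 | 18.7 | 23.3 |
| Poor responders leave verum, good responders leave sham | 25.1 | 26.1 | 30.2 | 30.3 | 37.9 |
| The reverse | 19.2 | 17.8 | 8.0 | 7.6 | 9.4 |

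With unrelated dropout the rules differ by 23.3 − 18.7 = 4.6 points. The large spreads need dropout that is linked to response in opposite directions in the two arms. The simulation keeps the week 4 mean level through weeks 5–8, which is what LOCF assumes, so it flatters LOCF.

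**The case against.** The strongest reply is that the word observed may be loose. The secondary responder outcome uses it in the same generic way, and with an imputed FAS named as the main analysis it could mean everyone in that group's analysis set. That reading is possible, so the denominator is a conflict on plain reading and not a proven available-case rule. The LOCF sentence has no such escape.

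It can also be said that the analysis plan, which the article says is fixed before the study starts, may settle the matter. That covers detail the article leaves out, such as a minimum number of valid diary days. It does not cover an instruction that the article gives and that contradicts itself.

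Three stronger inferences are tempting and should not be drawn:

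- **That the fixed divisor of 4 counts missing weeks as zero.** If missing weeks are imputed first and the window is then summed, the divisor agrees with the imputation rule. The article does not state that order, which merits a clarifying line, but it is not a third conflicting rule.
- **That a first-observation rule always makes an early leaver a non-responder in weeks 1–4.** Someone with 4 CSBMs in each of weeks 1 and 2 who then leaves scores (4+4+2b)/4 = 2 + b/2 with baseline carried. That is 2 to 3, and a response at b = 2. With the first post-baseline week carried the score is 4.
- **That the trial is biased by 9.5 points.** That figure needs 30% against 10% loss made up only of non-responders, and nothing in the article suggests this.

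Finally, counting dropouts as non-responders is itself a single imputation. In the simulation the closely related rule of scoring missing weeks as zero ranges from 7.6 to 30.3 points across the two opposed dropout patterns, against 19.2 to 25.1 for LOCF. This objection stands and is why the fix includes a sensitivity analysis.

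**Conclusion.** The point holds in this form. The imputation sentence contradicts itself, and for a wholly missing weeks 5–8 window its readings can give opposite responder status. Ordinary LOCF would also carry on-treatment data into the untreated window. The denominator wording, read plainly, does not fit the imputed FAS.

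The level of a responder rate shifts by 7.5 points (37.5% against 30%) in the assumed case of 12 responders and 8 dropouts. The between-arm difference shifts by only a few points unless dropout differs by arm and response. In one assumed data set the choice of rule moves p from 0.066 to 0.030. That shows significance can turn on the rule, not that it will. The direction and size in the actual trial cannot be known from the article.

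**What to change.** 1. In Clinical Data Analysis, delete the LOCF sentence. It also covers the other efficacy outcomes, so the analysis plan must give their rule.
2. In Primary Outcome Measurement and in item 1 of Secondary Outcome Measurement, make the denominator all FAS participants in the arm as randomised.
3. In the primary analysis, count participants with no evaluable four-week window as non-responders.
4. Add multiple imputation by arm as a sensitivity analysis, because non-responder counting is sensitive to differential dropout.
5. State that the division by 4 applies to complete windows, or follows the handling of missing weeks, so that missing weeks are not silently counted as zero.

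The cost is wording, slightly lower reported responder rates and a little more analysis work. No visit, treatment or data collection changes. The rule should be fixed before any outcome data are seen by arm.

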#### Gut Microbiota Analysis

The 16S rRNA third-generation full-length sequencing technology will be used to analyze the variations in intestinal microbiota (20–22). Sequencing will be performed on the V4 region and the V3 to V4 amplification region of the 16S rRNA gene. Purified amplicons will be pooled in equimolar amounts and paired-end sequenced (2 × 250) on an Illumina MiSeq 2500 platform (Illumina, San Diego, USA) according to standard protocols. After screening, the clean sequences will be clustered into operational taxonomic units (OTUs) based on 97% identity using Uparse (version 7.0.1001). Rarefaction curves for alpha diversity will be generated to assess the efficiency of sequencing depth. Species richness and diversity will be estimated using the observed species, Chao1, Shannon index, and Simpson index. Principle coordinate analysis and partial least-squares discriminant analysis will be used to reveal differences in OTU levels between samples. The linear discriminant analysis effect size will be performed using the non-parametric factorial Kruskal–Wallis sum-rank test to assess the effect size of each differential OUT.

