### Trial Design

This trial is designed as a randomized, sham-controlled trial with blinded participants, outcome assessor, and statistician. In this study, 80 eligible participants will be randomized to the verum acupuncture (VA) or sham acupuncture (SA) group with a ratio of 1:1. The total research period will be preceded by a 1-week run-in phase after the screening visit, then following the 4-week treatment phase, and 4-week follow-up phase. Forty healthy volunteers will also be enrolled to serve as a healthy control group. Healthy volunteers will not receive any treatment, and the correlation between gut microbiota and fecal miRNAs will be determined by comparing the constipated patients before treatment with them. The time frame of this trial is presented in Table 1.

**Table 1 T1:** Time points of treatment assessment.

	**Enrollment**	**Baseline**	**Treatment phase**		**Follow-up phase**			
**Time point**	**Week −1**	**Week 0**	**Week 2**	**Week 4**	**Week 5**	**Week 6**	**Week7**	**Week 8**

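### PLS-DA, one of two ordinations named to show OTU differences, separates groups on pure noise at these sample sizes unless it is validated

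*Protocol article*

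**What the plan says.** The Gut Microbiota Analysis section of the protocol article states that "the clean sequences will be clustered into operational taxonomic units (OTUs) based on 97% identity". It then gives two ordinations one shared purpose. The sentence opens with principal coordinate analysis and continues that "partial least-squares discriminant analysis will be used to reveal differences in OTU levels between samples". The next sentence names LEfSe, with a Kruskal-Wallis test for each differential OTU. Four alpha-diversity indices are listed as estimates.

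The section names no cross-validation or label permutation for PLS-DA, and no test of the community as a whole. It gives no number of OTUs.

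The group sizes come from elsewhere in the article. Under Trial Design, "80 eligible participants will be randomized to the verum acupuncture (VA) or sham acupuncture (SA) group with a ratio of 1:1", and patients before treatment are compared with healthy volunteers. Under Calculation of Sample Size, "the number of healthy volunteers will be 40 cases". Table 1 schedules the microbiota analysis at enrolment and at week 4. The natural contrasts are therefore 80 patients against 40 healthy volunteers at baseline, and verum (VA) against sham (SA) at week 4.

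**The concern.** Principal coordinate analysis ignores group membership. PLS-DA does the opposite: it looks for the directions in OTU space that best agree with the labels. When OTUs outnumber samples, such directions exist by chance alone. A clear gap between groups on the score plot is then what one expects under no difference, and the plot cannot do the job that the sentence gives it.

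At stake is how the microbiota comparison will be read. The other ordination in the sentence has no test attached, and LEfSe speaks to single OTUs. A reader who asks whether the community differs between groups would find the PLS-DA plot the most striking exhibit and the least informative one. The Discussion expects the trial to show that acupuncture works by modulating the exchange between miRNAs and microbiota, so the temptation to lean on such a plot is real.

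**Working it through.** **Inputs.** 40 per randomised arm and 40 healthy volunteers (Calculation of Sample Size). With the stated 20% drop-out, 40 × (1 − 0.20) = 32 completers per arm. The OTU count p is not given, so a range is assumed.

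**The plan's own figure.** The article states nothing on how PLS-DA performs. Its only relevant figure is the sample size. Taking its base of 30 cases as per group, 30/(1 − 0.20) = 37.5, so 38 per group or 76 in total, against the stated 40 and 80. The article says that no formula was available and adds an unquantified allowance for miRNA validation, so 80 cannot be reproduced strictly. Nothing below depends on how 80 was reached.

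**Why separation is expected.** With standardised data X (n samples, p OTUs) and labels y, the first PLS score is t ∝ XX′y. If the OTUs are independent noise, the expected squared correlation between t and y is roughly p/(p + n + 1). For n = 80:

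- p = 50: 50/131 = 0.38
- p = 100: 100/181 = 0.55
- p = 500: 500/581 = 0.86
- p = 1,000: 1,000/1,081 = 0.93

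Simulated values with independent normal data are 0.38, 0.57, 0.86 and 0.93. As p grows, the first axis becomes a copy of the labels.

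**Simulation under no difference.** Two-component PLS-DA, autoscaled, 30 to 60 data sets per cell. Entries are in-sample accuracy, with AUC in brackets. Counts are independent and overdispersed. The correlated case has ten shared factors carrying 50% of the variance.

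| OTUs | 40 v 40, counts | 32 v 32, counts | 80 v 40, counts | 40 v 40, correlated | 40 v 40, counts, 7-fold CV accuracy |
|---|---|---|---|---|---|
| 50 | 0.824 (0.905) | 0.875 (0.947) | not run | not run | 0.484 |
| 100 | 0.922 (0.977) | 0.959 (0.992) | 0.898 (0.955) | 0.857 (0.933) | 0.500 |
| 200 | 0.991 (0.999) | 0.994 (1.000) | 0.974 (0.995) | 0.914 (0.973) | 0.491 |
| 500 | 1.000 (1.000) | 1.000 (1.000) | 1.000 (1.000) | 0.957 (0.991) | 0.489 |
| 1,000 | 1.000 (1.000) | 1.000 (1.000) | 1.000 (1.000) | 0.971 (0.996) | 0.505 |

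For 80 against 40, assigning everyone to the larger group already scores 80/120 = 0.67, so AUC is the fairer measure there. Relative abundances instead of log counts give slightly lower accuracy at 100 OTUs (0.900 for 40 v 40, 0.853 for 80 v 40) and 0.995 or more at 500. With a third component, the correlated case for 40 v 40 reaches 0.999 or more from 500 OTUs.

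Across the equal-group settings with independent OTUs, 7-fold cross-validated accuracy is 0.45 to 0.51 and Q2 is negative (−0.05 to −0.72). Validation therefore removes the false separation.

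**The alternative.** PERMANOVA on Bray-Curtis distances (500 OTUs, 199 permutations, 400 null data sets, level 0.05) rejects in 5% of data sets at 32 per group and 4% at 40 per group. It holds its level.

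**The case against.** The strongest reply is that the article prescribes none of this misuse. It attaches no p-value, accuracy threshold or decision to PLS-DA, does not fix two components, and does not rule out cross-validation. The sentence speaks of differences between samples, not groups, which fits a pair of descriptive plots. A separate statistical analysis plan is mentioned under Clinical Data Analysis, and validation of PLS-DA is a detail often left to such a plan.

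Much of this stands. The simulated accuracy is a proxy for what the eye sees on an unvalidated plot, not a step in the plan. The missing community-level test is no error in itself in a condensed article. What remains is a positive statement: a label-driven method is named as a means to reveal differences, in a section detailed enough to give the clustering threshold and the test inside LEfSe. Without validation it cannot serve that purpose.

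A reader might go further in three ways that the document does not support:

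- **That PLS-DA is the only stated means.** Principal coordinate analysis stands beside it and does not share the fault, and LEfSe with Kruskal-Wallis follows as a per-OTU test.
- **That every microbiota contrast will show a difference whatever the truth.** This applies to the unvalidated PLS-DA display alone.
- **That the mechanistic claim rests on PLS-DA.** The Tripartite Network Analysis section uses Spearman correlations and states no PLS-DA input.

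**Conclusion.** The concern holds in a limited form. At 32 to 40 per arm, and at 80 against 40, unvalidated PLS-DA shows marked group separation where none exists, so its display cannot count as evidence of a group difference. The direction of the error does not depend on the OTU count; its size does. Separation is near-perfect from about 200 independent OTUs, clear but incomplete at 50, and somewhat weaker with correlated OTUs.

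The result rests on the assumed range of OTU counts, on simulated rather than real abundance data, and on PLS-DA being shown without validation. The primary and secondary clinical outcomes, the LEfSe results and the Spearman network are untouched.

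**What to change.** In Gut Microbiota Analysis, name PERMANOVA as the community-level comparison, on the distance matrix that principal coordinate analysis already requires. Use it for patients against healthy volunteers at baseline, and for VA against SA at week 4 with baseline taken into account, for example through baseline coordinates as covariates. Because PERMANOVA can also react to unequal spread, above all with 80 against 40, report a check of within-group dispersion beside it.

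Label PLS-DA as descriptive. Otherwise report it only with cross-validated Q2 or error and a label-permutation p-value, and repeat the whole fit, including any choice of components, within each fold and permutation.

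The cost is a sentence or two and slight extra computing, with no new samples. The downside for the authors is that some apparent separations will disappear.

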#### MicroRNAs High-Throughput Sequencing Analysis

High-throughput sequencing using stool samples will be performed for miRNA expression profiling to determine candidate miRNA biomarkers for the efficacy of acupuncture (24–26). Fecal miRNA levels initially will be determined using a TaqMan low-density array in pooled samples. Markedly altered miRNAs in participants will subsequently be validated using quantitative real-time polymerase chain reaction on individual samples. Agilent 2100 will be used for detection, and after qualification, these fragments will be sequenced using the Illumina NOVA platform. Bowtie software will be employed to classify and annotate sRNA, and unannotated reads will be obtained by comparing clean reads with the database. The difference between SCC patients and healthy volunteers at baseline will be analyzed to explore potential biomarkers associated with the development of SCC. Within the pool of biomarker candidates related to SCC, the difference between VA and SA at week 4 will be compared, to determine biomarkers related to the clinical efficacy.

#### Tripartite Network Analysis

The tripartite network analysis will be used to integrate information from the fecal microRNA characteristics, specific gut microbiota, and clinical data for constipated patients in the VA and SA groups. The interaction among the clinical efficacy (amelioration of SCC symptoms), microRNA characteristics (the differential expression of miRNAs in the stool), and fecal microbiome (stool microbial community) will be investigated by computing Spearman's correlations in Matlab (version R2015b). An effect size of *r* = 0.10 is considered less (1% variance explained), 0.30 moderate (9% variance explained), and 0.50 large (25% variance explained). Fisher's *r*-to-*z* transformation will be adopted to investigate the correlation coefficient difference between groups (acupuncture-sham acupuncture), using the *Z*-test. Significance will be considered at uncorrected *p* < 0.05. The Cytoscape (version 3.8.2) will be used to generate and visualize the phenome, fecal microbiome, and differentially expressed miRNAs interaction network. The networks will be presented based on selecting the gut microbiota counts and their first neighbors as nodes and all adjacent edges. The results will be shown in the line with direct (correlations with fecal microbiome) and indirect effects (clinical symptoms and differentially expressed miRNAs) with an emphasis on the association between microbiome and clinical efficacy. The comparisons between groups will be analyzed using one-way analysis of variance and independent sample *t-*test.

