## Abstract

**Background:**

Severe chronic constipation (SCC) is a common functional gastrointestinal (GI) disorder associated with disruptions in GI motility. Abnormalities between gut microbiota and microRNAs (miRNAs) are implicated in the pathogenesis of GI motility in SCC. Acupuncture has been shown to improve constipation-related symptoms and rebalance the gut microbiota. This protocol proposed a plan to explore the hypothesis that the efficacy of acupuncture is associated with the crosstalk between gut microbes and miRNAs in patients with SCC.

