## Methods

### Objectives

This trial aims to (1) re-evaluate the pure therapeutic effect of acupuncture for SCC; (2) identify the correlation between the gut microbiota and fecal miRNAs in patients with SCC; and (3) investigate the interactions among acupuncture-induced improvement of constipation symptoms, changes of fecal miRNAs and regulation of intestinal microbiota.

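### The planned comparison of verum and sham correlations tests effect modification by arm, so it cannot show whether acupuncture's benefit runs through miRNAs or microbes

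*Protocol article*

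**What the plan says.** The Abstract sets out to "explore the hypothesis that the efficacy of acupuncture is associated with the crosstalk between gut microbes and miRNAs in patients with SCC". The third item under Objectives is to "investigate the interactions among acupuncture-induced improvement of constipation symptoms, changes of fecal miRNAs and regulation of intestinal microbiota". The closing sentence of the Discussion goes further: it expects the trial to demonstrate that efficacy comes about through altering the miRNA–microbiota crosstalk.

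Under Tripartite Network Analysis, the relations among clinical efficacy, miRNAs and microbiome "will be investigated by computing Spearman's correlations in Matlab (version R2015b"). The two arms are then brought in by Fisher's method: this "transformation will be adopted to investigate the correlation coefficient difference between groups (acupuncture-sham acupuncture"), with a Z-test. "Significance will be considered at uncorrected" p < 0.05. The section ends with ANOVA and t-tests between groups, without naming the variables.

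Two other sections bear on the point. MicroRNAs High-Throughput Sequencing Analysis compares candidate miRNAs between verum (VA) and sham (SA) at week 4. Gut Microbiota Analysis describes differences between samples but names no VA–SA test for taxa.

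**The concern.** The null hypothesis of the r-to-z test is that a marker and the symptom change are equally correlated in both arms. Rejecting it says that the arm modifies the association. A pathway claim needs something else: that acupuncture changes the marker, and that the marker change goes with symptom change once arm is accounted for.

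Suppose acupuncture raises a marker by a similar amount in every patient and the marker drives symptoms in the same way in both arms. The marker level then differs between arms, but the correlation does not. The one stated between-arm test of the marker–symptom link would find nothing, although the pathway is real. In the other direction, a correlation depends on the spread of the marker as well as on the slope, so the test can reject when the average marker level is the same in both arms. Either result could be misread when Objective 3 is reported.

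**Working it through.** **Inputs from the protocol.** Spearman correlation; Fisher r-to-z with a Z-test; alpha 0.05, uncorrected (two-sided assumed, as the protocol does not say). Benchmarks for r include "0.30 moderate (9% variance explained), and 0.50 large (25% variance explained"), so 0.30 and 0.50 are used below. Sample size: "plus a drop-out rate of 20%, the sample size in this setting is determined to be 80 cases (40 per").

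**The plan's own figure.** No power is given for this test. The starting point is that "the sample size is mainly 30 cases to obtain outcomes with statistical significance". Read as per arm, which the text does not state, 30/(1 − 0.20) = 37.5, so 38, close to the stated 40; the section also cites an allowance for miRNA validation. With 20% drop-out from 40, 40 × 0.80 = 32 remain. Both 40 and 32 per arm are used.

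**Model (assumed).** Marker M = a·arm + error; symptom change Y = b·M + error; unit-variance errors; no direct effect of arm, so mediation is full when a and b are both non-zero. b = 0.315 gives r = 0.315/√(0.315² + 1) = 0.30; b = 0.577 gives r = 0.50. Test statistic: Z = (atanh r_VA − atanh r_SA)/√(2/(n − 3)). The comparator is a joint test: a t-test of M by arm, and a regression of Y on M adjusted for arm, both at 0.05. There were 20,000 runs per setting.

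**1. Constant shift, common slope, equal variances.** Adding a constant to M in one arm leaves r unchanged, so the expected difference in atanh r is 0.

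| n per arm | a (SD) | r | r-to-z rejects | joint test rejects |
|---|---|---|---|---|
| 40 | 0.8 | 0.30 | 5.1% | 73% |
| 40 | 0.8 | 0.50 | 5.8% | 94% |
| 32 | 0.8 | 0.30 | 5.3% | 60% |
| 32 | 0.8 | 0.50 | 5.5% | 87% |

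Over a = 0.5 to 1.0 SD, r-to-z rejects 5.1% to 5.8% at 40 per arm and 5.2% to 5.9% at 32. With no mechanism at all (a = 0, b = 0) it rejects 4.7% and 4.9%, so it hardly separates the two situations. At a = 0.5 and r = 0.30 the joint test reaches only 46% at 40 per arm. Using rank regression in the joint test (a separate run of 3,000 replicates) gives 68% and 94% at 40 per arm and 55% and 87% at 32, for a = 0.8 and r = 0.30 and 0.50. When a or b is zero, the joint test rejects 0.3% to 5.0% of the time.

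**2. Individual response varies in VA** (mean shift 0.8 SD, sham r = 0.50).

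| SD of individual shift | r-to-z, n = 40 | joint, n = 40 | r-to-z, n = 32 | joint, n = 32 |
|---|---|---|---|---|
| 0.5 | 6.7% | 91% | 6.5% | 84% |
| 1.0 | 13.4% | 82% | 12.2% | 73% |
| 1.5 | 32.5% | 69% | 26.7% | 58% |

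**3. Same mean marker level, different spread.** Slope 0.6 in both arms and marker SD s times larger in one arm, so r = 0.6s/√(0.36s² + 1).

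- s = 1: r = 0.514, atanh r = 0.569.
- s = 1.5: r = 0.669, atanh r = 0.809, difference 0.240.
- s = 2: r = 0.768, atanh r = 1.016, difference 0.447.

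At 40 per arm the standard error is √(2/37) = 0.2325, so the standardised differences are 1.03 and 1.92, and the normal approximation gives 18% and 48% rejection. Simulation with Spearman gives 18% and 45% at 40 per arm, and 15% and 37% at 32.

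**4. What r-to-z does detect.** If acupuncture does not move M but r is 0.50 in VA and 0 in SA, it rejects 62% at 40 per arm and 52% at 32. That is effect modification.

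**The case against.** Much of what is needed is already planned. The miRNA section compares candidates between arms at week 4, and in the simulations a plain t-test on the marker has 94% power for a 0.8 SD shift at 40 per arm. The network section opens with marker–symptom correlations in patients of both arms. A reader might infer that r-to-z is the only between-arm test of mechanism in the protocol; those comparisons, and the ANOVA and t-tests that close the network section, show that it is not. This stands. What is missing is arm adjustment, a rule joining the two steps, and a named VA–SA test for taxa.

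A reader might also infer that the r-to-z null is true exactly when the pathway is real. That fails both ways: the null also holds when there is no mechanism, and under mediation it needs a constant shift, a common slope and equal variances. Step 2 of the working shows how far rejection rises without them.

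Nor should step 3 be read as rejection without any effect of acupuncture. In randomised arms a true difference in spread after treatment is itself an effect on the marker; only the mean effect is zero. The protocol gives no spread ratio, so 1.5 and 2 are illustrations.

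Finally, the Abstract speaks of association and the Objectives of interactions, and whether acupuncture alters miRNA–microbe coupling is a fair question for r-to-z. This too stands. It does not cover the Discussion's closing claim, which is one of mediation.

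**Conclusion.** The point holds in a limited form. The stated between-arm test of the marker–symptom link answers a question about effect modification, and no stated step combines an arm effect on the marker with an arm-adjusted marker–symptom association. Under full mediation with a constant shift, the test rejects at about 5%, against 46% to 99% for the joint test at 40 per arm (shifts of 0.5 to 1.0 SD, r of 0.30 or 0.50). With varied response it rejects up to about a third of the time, still less often than the joint test.

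These figures assume normal data, one pre-selected marker, no direct effect of arm and single-test alpha of 0.05; the shifts are not from the protocol. The analysis is secondary and exploratory, and the primary outcome is not touched. The change is worth making because it lets the data already planned address Objective 3.

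**What to change.** Under Tripartite Network Analysis, state for Objective 3 that, for each selected miRNA and taxon, the analysis will:

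- (a) test the VA–SA difference in marker change from baseline to week 4;
- (b) test the association of marker change with symptom change in all randomised patients, with arm as a covariate (partial Spearman or rank regression);
- call a marker a candidate pathway only if both hold.

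Keep the r-to-z comparison, labelled as an exploratory check of effect modification and not read as evidence for or against the pathway. Reword the last sentence of the Discussion to speak of a candidate pathway or an association: the marker is not randomised, so even (a) and (b) together do not prove mediation.

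The cost is a wording change, with no new samples, visits or patients. The small downside is that (b) assumes a common slope in both arms, which the retained r-to-z test or an arm-by-marker term can check.
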